### Ethical Approval and Trial Registration

The study received ethics approval from the University of Auckland Human Participant Ethics Committee on June 18, 2020 (Ethics Committee reference: 024542). The protocol for the RCT was prospectively registered with the Australian New Zealand Clinical Trials Registry on April 17, 2020 (ACTRN12620000516987).

### Intervention: Whitu: 7 Ways in 7 Days

The intervention has been developed as a cross-platform app; therefore, it will function on both Android and iOS operating systems. Data or internet connectivity is required to stream the informational videos contained in each module. The app is free to download. No user information or app analytics data are collected or stored over the internet. Any data input by the user are stored locally on the user’s device in an unencrypted SQLite database. These data can be safely deleted at any time by the user via the system settings on the device or by deleting the app.

Evidence shows that young people often do not use health apps for long periods; for example, one review of 93 health apps found that only 3.9% of people who downloaded these apps used them for a median of 15 days [47], and another review of 10 self-help interventions for anxiety and depression found that only 0.5% to 28.7% of users completed the interventions [48]. Therefore, the Whitu app has been purposely designed to be completed over the course of one week. The user receives daily push notifications reminding them to complete at least one module per day and to practice preferred exercises from previous modules. Many CBT-based, psychoeducational, and positive psychology interventions focus on teaching a repertoire of coping strategies and techniques to allow users to choose from a broad range of strategies and discover which ones work best for them individually. In a similar fashion, our aim in offering seven modules is to ask participants to try all the modules over the course of one week and keep practicing the strategies that work best for them. The seven modules are described in detail in Table 1.

**Table 1 table1:** The seven modules included in the Whitu: 7 Ways in 7 Days app.

Module	Description
Module 1: Feel	The first module acknowledges that young people may be feeling low and struggling with negative emotions due to COVID-19. The module introduces the concept of identifying and monitoring emotions and recognizing adaptive and maladaptive coping skills. Exercises include recognizing and rating recent emotions as well as grouping coping skills into adaptive and maladaptive categories.
Module 2: Relax	The second module recognizes the uncertainty and stress that young people may be feeling due to the COVID-19 pandemic. The module introduces common relaxation techniques to manage stressful situations. Exercises including deep breathing, progressive muscle relaxation, and visualization.
Module 3: Be kind to yourself	The third module introduces the concept self-compassion and includes a short check-in meditation. The module then asks participants to be mindful of a hard feeling they have had in the past week, reflect on whether friends and family have felt the same, and write self-kindness statements.
Module 4: Be thankful	The fourth module introduces the concept of gratitude and how it is linked to positive well-being. This module encourages grateful contemplation and action by asking users to list things they are thankful for daily and in different situations and to keep a written or photographic record of things they are thankful for.
Module 5: Connect	The fifth module recognizes the negative impact that lockdowns as well as physical distancing can have on relationships. The module introduces the importance of social connection for well-being. It encourages participants to identify important people in their lives and to practice ways of staying connected with them.
Module 6: Look after your body	The sixth module discusses how the COVID-19 situation makes it more difficult to stay active and look after our bodies. This module introduces how eating well, moving regularly, and getting rest support psychological well-being. Information is provided about the key food groups, benefits of physical activity, and sleep. Participants are encouraged to plan how to improve their diet, increase their physical activity, and get more sleep.
Module 7: Set goals	The seventh module acknowledges that the COVID-19 pandemic has likely interrupted users’ routines and made it harder to set healthy goals. This module introduces goal setting and guides the user to set their own specific, measurable, achievable, realistic, and time-based (SMART) goals. Explores benefits and barriers to setting different goals and helps the user build confidence by identifying various factors that impact the process of achieving their particular goal.

#### Onboarding

When the user first opens the app, they are presented with a splash screen containing the app logo, the app title, and a welcome message. This is followed by a screen where the user can input their name. This name is used to personalize messages and exercises throughout the app. The user is then presented with four Onboarding screens, including a welcome message and a brief explanation of the features of the app (see Figure 2).

**Figure 2 figure2:**
[figure not shown]
Screenshots of the onboarding process of the Whitu: 7 Ways in 7 Days app.

#### Badges

Users earn badges as they complete modules and revision exercises. The aesthetics of the badges are inspired by Māori and Pacific design motifs. Earned badges will appear in color on the Badges screen, while unearned badges appear greyed out. Users can collect a total of 20 badges.

#### Videos

Each module contains at least one informative video that provides a graphical and audio description of its content. The videos are narrated by two characters, Ana and Ben.

#### Exercises

Each module contains one or more exercises that demonstrate the well-being concepts and techniques described in the videos. For example, in Exercise 1 of Module 1, users are asked to identify and select various emotions they may have experienced over the past week (Figure 3).

**Figure 3 figure3:**
[figure not shown]
Screenshots of the Identifying Emotions exercise from Module 1 of the Whitu: 7 Ways in 7 Days app.

#### Completed Modules

When users have viewed all videos and completed all exercises in a module, they are able to review the content of the module or carry out revision exercises intended to refresh and reinforce the message of each module. Users earn badges for each revision exercise they complete (see Figure 4).

**Figure 4 figure4:**
[figure not shown]
Screenshots of the seven modules and associated badges of the Whitu: 7 Ways in 7 Days app.

#### Revision Exercises

Each module has one or more associated revision exercises that only become available after the module is completed. For some modules, the same revision exercise can be repeated across multiple days. For example, the revision exercise for Module 1 is a condensed version of the main module content that users can use to track their feelings over two days.

### Outcome Measures

Outcome measures will be assessed at baseline, 4 weeks after baseline, and 3 months after baseline. Demographic data, including sex, age, ethnicity, and pre-existing mental health conditions, will be collected at baseline via self-report on REDCap. All the outcome measures listed below are brief and have acceptable reliability and validity. Completing the questionnaires at each time point will take approximately 20-30 minutes.

#### Primary Outcomes

##### 1. Emotional Well-Being

This outcome will be assessed via the WHO-5 [45]. The WHO-5 is a 5-item scale that assesses positive emotional well-being (eg, “I have felt cheerful and in good spirits”). Participants are asked to indicate the extent to which each item matches how they have been feeling over the past two weeks on a 6-point Likert scale ranging from 0 (“at no time”) to 5 (“all of the time”). The final score is calculated by summing the five responses and multiplying the total by four. This gives a percentage score ranging from 0-100, with 0 representing the worst possible well-being and 100 representing the best possible well-being. The internal consistency of the WHO-5 demonstrates good reliability (α=.84) in children and adolescents [49].

##### 2. Mental Well-Being

This outcome will be assessed by the Short Warwick-Edinburgh Mental Well-being Scale (SWEMWBS) [50,51]. The SWEMWBS is a short version of the 14-item Warwick-Edinburgh Mental Well-Being Scale (WEMWBS), which is comprised of positively worded items measuring different aspects of positive mental health [41]. The SWEMWBS is a 7-item scale that asks participants to rate their experience of a range of thoughts and feelings (eg, “I’ve been dealing with problems well”) over the last two weeks on a 5-point Likert scale ranging from 1 (“none of the time”) to 5 (“all of the time”). The score is calculated by summing individual ratings and transforming the total into a metric score using a transformation provided by the scale authors. Scores range from 7 to 35, with higher scores indicating greater positive mental well-being. The original scale has demonstrated good content validity and is correlated with other mental health and well-being measures [50]. The short version has demonstrated similar reliability and validity to the full version (α=.84) and is suitable to be used by adolescents [52,53].

#### Secondary Outcomes

##### 1. Depression

This outcome will be assessed by the short version of the Centre for Epidemiological Studies Depression Scale (CES-D) [54]. The CES-D is a 20-item scale designed to measure depressive symptoms in the general population. Participants are asked to rate on a 4-point Likert scale how often they have experienced a variety of different feelings or behaviors (eg, “My sleep was restless”), ranging from 0, rarely or none of the time (less than 1 day) to 3, most or all of the time (5-7 days). Scores are calculated by reverse scoring positive items and summing item totals, yielding a total score between 0 and 60. Higher scores indicate more depressive symptoms. The scale has demonstrated excellent internal consistency (α=.85) and demonstrates high correlations with other depression measures [54].

##### 2. Anxiety

This outcome will be assessed by the Generalized Anxiety Disorder seven item scale (GAD-7) [55]. The GAD-7 is a 7-item self-report scale assessing how often participants experience different symptoms of anxiety (eg, “feeling nervous, anxious, or on edge”). Items are rated on a 4-point Likert scale including 0, not at all; 1, several days; 2, more than half the days; and 3, nearly every day, yielding one total score. Scores of 5, 10, and 15 represent cutoffs for mild, moderate, and severe anxiety, respectively. This scale has been demonstrated to be capable of identifying probable cases of generalized anxiety disorder. It demonstrates excellent reliability (α=.92) and validity [55] in a general population [56] and in adolescents [57].

##### 3. Stress

This outcome will be assessed by the 10-item Perceived Stress Scale (PSS-10) [58,59]. The PSS-10 is a 10-item scale that assesses the extent to which individuals have felt a range of stressors over the last month. Participants are asked to rate how often they experienced different stressful thoughts and feelings (eg, “In the last month, how often have you felt that you were unable to control the important things in your life?”) on a 5-point Likert scale ranging from 0, never, to 4, very often. A total score is calculated by reverse scoring items 4, 5, 7, and 8 and summing all ten of the responses. Scores below 13 are considered to indicate low stress, scores between 14 and 26 are considered to indicate moderate stress, and scores between 27 and 40 are considered to indicate high stress. The PSS-10 scale has superior psychometric properties relative to other existing perceived stress scales and has demonstrated good reliability and validity [60].

##### 4. Self-Compassion

This outcome will be assessed using the Self-Compassion Scale–Short Form (SCS-SF) [61].The SCS-SF is an alternative to the long form Self-Compassion Scale [62]. The SCS-SF comprises 12 items that ask participants to rate how they typically act toward themselves in different situations (eg, “When I’m going through a very hard time, I give myself the caring and tenderness I need”) on a 5-point Likert scale ranging from 1, almost never, to 5, almost always. The SCS-SF has six subscales (overidentification, self-kindness, mindfulness, isolation, common humanity, and self-judgement) comprising two questions each. Scores are calculated by reverse scoring the negative subscale items, calculating the mean for each subscale, and computing a total mean. Higher scores indicate greater levels of self-compassion. The SCS-SF demonstrates good reliability (α>.86), is highly correlated with the long form scale [49], and has shown adequate reliability in an adolescent sample [63].

##### 5. Sleep

This outcome will be assessed using a single-item Sleep Quality Scale (SQS) [64]. This single-item questionnaire (“During the past 7 days, how would you rate your sleep quality overall?”) is assessed on an 11-point visual analog scale (VAS) from 0-10. The VAS scores are anchored with 0, terrible; 1-3, poor; 4-6, fair; 7-9, good; and 10, excellent. The SQS has demonstrated excellent concurrent and convergent validity with other lengthier sleep scales and has been deemed to be effective in determining clinically meaningful changes in sleep quality [64].

##### 6. User Engagement

This outcome will be assessed via two subscales (App Subjective Quality, Perceived Impact) of the end-user version of the uMARS [65]. The uMARS is a self-report scale designed to assess the quality of health apps. The Subjective Quality score for the app is derived from four items that determine user experience (eg, “Would you recommend this app to people who might benefit from it?”). These items are scored on a 5-point Likert scale ranging from 1 to 5; however, each has different anchors. Scores from this subscale can be reported individually or as a mean total. The Perceived Impact score consists of six items that measure the impact of using the app on knowledge, attitudes, and intentions. The six items are reported as individual items and measured on a Likert scale ranging from 1 to 5 (1, strongly disagree; 5, strongly agree). The uMARS demonstrates good internal reliability overall (α=.90), and the two subscales demonstrate good to moderate reliability (α=.71 and .80) [43]. The scale also contains an open-ended question that asks: “Do you have any further comments about the app?”

In addition to the uMARS, participants will also be asked the following questions about their use of the Whitu app: (1) How many modules did you complete? (2) On how many days did you use the app? (3) What module was the most useful? Why? (4) What did you like about the app? (5) How can we make the app better for young people in the future? and (7) Did you experience any technical difficulties with the app? If yes, what happened?

#### Hypotheses and Statistical Analyses

It is predicted that the Whitu app group will demonstrate improved well-being (increased emotional and mental well-being), increased self-compassion, and improved sleep at 4-week and 3-month follow-up compared to the wait-list control group. We also hypothesize that the Whitu app group will demonstrate decreased stress, depression, and anxiety at 4-week and 3-month follow-up compared to the wait-list control group.

Data will be analyzed in SPSS (IBM Corporation) or SAS (SAS Institute). Prior to any data analysis, the data will be tested for violations of statistical assumptions and screened for errors and outliers. If parametric assumptions are not met due to nonnormality, transformations or nonparametric tests will be used. Pearson correlations (or Spearman ρ if nonnormal) will be used to explore the relationships between the outcome measures and demographic characteristics and other psychosocial factors. ANOVAs or Kruskal-Wallis tests (if nonnormal) will be used to explore associations between categorical variables and outcome measures. Linear mixed models will be used to determine whether changes in psychological outcomes are the result of the interaction between the intervention group and time, with post-hoc tests to assess pairwise comparisons of groups at each time point and within-group changes over time. Linear mixed models also allow for missing data, as they enable all participants with baseline data to be included in the analysis. We will also examine possible 3-way interactions with age, sex, or ethnicity (eg, age*group*time). Means, SDs, and CIs will be presented with the analysis. Data will be subjected to both intention-to-treat and per-protocol analyses. Per-protocol analyses will include participants who report completing all seven modules. Study results will be disseminated through peer-reviewed journals and conferences.

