### Power Calculation

A previous study of a web-based positive psychology intervention for mildly depressed adults [44] found a between-group improvement in well-being (effect size of *f*=0.155) using the World Health Organization-Five Well-Being Index (WHO-5) [45]. Using G*Power [46], we calculated that the minimum required sample size to detect an effect size of *f*=0.155 using a mixed analysis of variance (ANOVA) including within-subject (3 time points) and between-subject (2 groups) effects with 90% power and at a 2-sided 5% significance level was 90 participants (45 per treatment arm). To ensure cultural acceptability, we will aim to recruit at least 40% Māori and Pacific young people (n=36).

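### Free improvement: estimate the 4-week and 3-month group differences with baseline adjustment, and report within-group changes descriptively

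*Protocol article*

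**What the plan says.** The Outcome Measures section sets three occasions: "Outcome measures will be assessed at baseline, 4 weeks after baseline, and 3 months after baseline". Under Hypotheses and Statistical Analyses, every directional hypothesis is a comparison with the wait-list arm at 4 weeks and 3 months.

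The lead analysis is a linear mixed model used to judge whether "changes in psychological outcomes are the result of the interaction between the intervention group and time". It is followed by "post-hoc tests to assess pairwise comparisons of groups at each time point and within-group changes over time". Mixed models are also favoured because "they enable all participants with baseline data to be included in the analysis", so baseline enters as a response rather than as a covariate.

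The Power Calculation section takes the same view of the data. The test behind it is described as follows: "mixed analysis of variance (ANOVA) including within-subject (3 time points) and between-subject (2 groups) effects". The target is 90% power at the two-sided 5% level, and the result is 45 participants per arm. No correlation between occasions is given.

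**The concern.** The questions are about group differences at two follow-up times. Two kinds of between-group quantity are planned, and neither is the most precise answer.

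- **Post-hoc group comparisons.** In a model with a free group-by-time term, the contrast at a follow-up time is in essence the raw difference in means. Chance imbalance at baseline carries through to it.
- **Interaction.** It does use baseline, but through change from baseline. That over-corrects whenever the correlation is below 1. As an omnibus test on 2 degrees of freedom, it also does not say at which time the arms differ.

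Two further tests add little. Taken literally, comparing groups at each time point includes baseline, where randomisation already makes any difference a chance one. Within-group change is not a randomised comparison: in an unblinded trial with self-reported scales during a pandemic, it mixes any app effect with regression to the mean and changing circumstances.

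At stake is precision in a trial of 45 per arm, and clarity about which estimate answers each hypothesis.

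**Working it through.** **Inputs.** From Power Calculation: f = 0.155, 90% power, two-sided 5%, 2 groups, 3 occasions, N = 90. The correlation r between occasions is not stated, so it is an assumption, varied below.

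**1. Reproducing N = 90.** For the within-between interaction in a repeated-measures ANOVA (sphericity assumed), the noncentrality is λ = f² × N × m / (1 − r), with m = 3 and degrees of freedom 2 and 2(N − 2). At r = 0.5 and N = 90:

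λ = 0.024025 × 90 × 3 / 0.5 = 12.97, power 0.902.

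The smallest N in equal arms that reaches 90% is 126, 108, 90, 72, 56 and 38 for r = 0.3, 0.4, 0.5, 0.6, 0.7 and 0.8. Of these, only r = 0.5 gives the stated 90. The between-groups version of the test would need 294 at r = 0.5, so it was not the one used.

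**2. What each planned contrast estimates.** In a mixed model fitted to one complete simulated data set, the group contrast at follow-up was 0.1441 and the raw difference in follow-up means was 0.1441. The group-by-time coefficient was −0.0298 and the difference in mean change was −0.0298.

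**3. Relative variance of a follow-up group contrast.** Raw: 1. Difference in change: 2(1 − r). Baseline-adjusted: 1 − r².

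| r | raw | change | adjusted | saving vs raw | saving vs change |
|---|---|---|---|---|---|
| 0.3 | 1 | 1.40 | 0.91 | 9% | 35% |
| 0.4 | 1 | 1.20 | 0.84 | 16% | 30% |
| 0.5 | 1 | 1.00 | 0.75 | 25% | 25% |
| 0.6 | 1 | 0.80 | 0.64 | 36% | 20% |
| 0.7 | 1 | 0.60 | 0.51 | 49% | 15% |

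For any r strictly between 0 and 1, 1 − r² is below both 1 and 2(1 − r). At r = 0.5 the standard error falls by 1 − √0.75 = 13.4%, and 90 participants carry the information of 90 / 0.75 = 120 analysed without adjustment. In 20,000 simulated trials of 45 per arm at r = 0.5, the variance ratios were 0.752 against raw and 0.766 against change.

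**4. Power at the planning effect.** Assume no difference at baseline and the same difference d (in SD units) at both follow-ups, with r = 0.5. Each change score has variance 1 and the two have covariance 0.5, so λ = (45/2) × d² × 2/(1 + 0.5) = 30d². Setting 30d² = 12.97 gives d = 0.658.

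- Unadjusted contrast at one time: SE = √(2/45) = 0.211, noncentrality 0.658/0.211 = 3.12, power 87%.
- Planned 2-df interaction: power 90% (step 1).
- Adjusted contrast at one time: SE = √(2 × 0.75/45) = 0.183, noncentrality 0.658/0.183 = 3.60, power 95%.

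Like for like on 2 degrees of freedom, a common-baseline model has λ = 45d² = 19.46 and power 98%, against 90% for the planned interaction.

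**The case against.** The strongest reply is that the lead test already uses baseline, since the interaction compares change between arms. That is correct. A reader might infer that the plan ignores the baseline score altogether, and the article does not support this: only the post-hoc follow-up contrasts leave it out, and only strictly so with complete data. With dropout, a likelihood-based mixed model draws on baseline through the within-person covariance. At d = 0.66 the interaction is also slightly more powerful than the unadjusted single-time contrast (90% against 87%), so the fair gain over the lead test is about 90% to 95%.

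The size of the saving is also not a fact of this trial. It rests on r = 0.5, back-solved from N = 90, which is a planning value and not evidence about these scales.

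A reader might further infer that efficacy will be claimed from improvement within the app arm. The article does not say so: its hypotheses are all between-group, and the within-group tests are post-hoc. The risk is one of misreading.

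Finally, covariate lists are often left to an analysis plan. This point concerns the model and contrasts that the article does state. If a fuller plan already adjusts for baseline, only the article's description needs aligning.

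**Conclusion.** The point holds as an improvement in efficiency and clarity, not as an error of validity. Both planned between-group quantities are unbiased under randomisation, and both are less precise than a baseline-adjusted contrast at any correlation strictly between 0 and 1. At r = 0.5 the loss is a quarter of the variance, or 13% of the standard error; step 3 gives the range for other correlations. The power figures also assume a constant follow-up difference, equal variances and complete data.

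Two stronger conclusions should not be drawn. The sample size is not wrong: 90 reproduces for the test that was planned. Nor does the argument make 4 weeks the primary time, because the article gives 4 weeks and 3 months equal standing and ranking them would be a separate design decision.

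**What to change.** - Use a constrained longitudinal mixed model with a common baseline mean in both arms and unstructured covariance. Alternatively, model the 4-week and 3-month scores with baseline-by-time as a covariate. The constrained model keeps everyone with baseline data in the analysis, which the article values.
- Report the adjusted group difference with a 95% CI at both 4 weeks and 3 months, as planned contrasts rather than post-hoc tests.
- Drop the between-group test at baseline.
- Present within-group changes descriptively, without p-values.

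The cost is analysis wording only. Under Procedures for the randomised trial, all participants complete the baseline questionnaires before randomisation, so no new data, visits or participants are needed.

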#### Procedures

Participants will be recruited from web-based communities (eg, social media) by an advertisement or flyer with a link to the REDCap site. On REDCap, interested participants will be screened for eligibility. If eligible, they can read and download the Participant Information Sheet, provide web-based consent, and complete the baseline questionnaires once they have consented. Once participants have consented and completed the baseline questionnaires, they will be randomized into either the intervention group (Whitu app) or wait-list control group. Randomization will occur using REDCap’s randomization module. Participants and research staff will not be blinded to treatment allocation. The wait-list control group will receive the app 3 months after the initial app group. Figure 1 shows the CONSORT flow diagram.

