**Figure 1 figure1:**
[figure not shown]
CONSORT (Consolidated Standards of Reporting Trials) flow diagram of participant recruitment, randomization, and attrition.

After randomization, the wait-list group will be informed that they are in the wait-list control group on REDCap. The intervention group will be shown a link and instructions on how to download the Whitu app on REDCap. During the first four weeks, participants in the intervention group will receive 2 emails reminding them to complete the app modules and an SMS text message asking them to confirm whether they have been able to download the app. Four weeks after completing the baseline questionnaires, participants in both groups will receive an email with a link to the first follow-up questionnaire on REDCap. Three months after baseline, both groups will receive an email with the link to the final follow-up assessment. After the wait-list control group completes the 3-month assessment, REDCap will send each group member an automated email with instructions on how to download the Whitu app. We will not follow up with the wait-list control group after they receive the app at the 3-month time-point.

All participant outcome data (eg, demographic data and psychological outcomes) will be collected via REDCap. We will not collect any information via the app, and any user input (eg, first name, responses to exercises) will only be stored locally on the user’s device. Only the Principal Investigators and research assistants ([name]) will have access to the participant data collected over REDCap. When the data are exported from REDCap, all data will be deidentified and stored separately from the participants’ information.

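### The per-protocol rule (all seven modules completed) cannot be met by wait-list controls, so as written that analysis has no control arm; applied to the app arm only, it is not a randomised comparison

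*Protocol article*

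**What the plan says.** Under Hypotheses and Statistical Analyses, the article states: "Data will be subjected to both intention-to-treat and per-protocol analyses". The per-protocol population is then defined: "Per-protocol analyses will include participants who report completing all seven modules". That section gives no separate criterion for the wait-list arm.

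The Phase 2 Procedures fix when controls can use the app: "The wait-list control group will receive the app 3 months after the initial app group". The text after Figure 1 puts this after the final assessment: "After the wait-list control group completes the 3-month assessment, REDCap will send each group member an automated email", with instructions for downloading the app. It adds: "We will not follow up with the wait-list control group after they receive the app at the 3-month time-point".

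Module completion is known only from a question to participants, listed under User Engagement: "1) How many modules did you complete". The Intervention section confirms that there is no objective record: "No user information or app analytics data are collected or stored over the internet". The same section cites a review of ten other self-help interventions in which "only 0.5% to 28.7% of users completed the interventions".

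**The concern.** A per-protocol set should describe adherence in each arm to that arm's own assignment. This rule describes adherence to the app only. Read literally, it empties the control arm. Read charitably, it keeps all controls and drops app participants according to something they did after randomisation.

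People who finish seven self-help modules may well be more motivated or have a better outlook than those who stop. A completers-versus-controls contrast can then favour an app that does nothing. Participants are unblinded and report both their completion and their outcomes, which adds to the worry. Because the text permits two incompatible sets, the choice could also be made after the data are seen.

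**Working it through.** **1. The rule against the schedule.** The rule requires a report of seven completed modules. Controls are sent the app after the 3-month assessment and are not followed after that. A control following the protocol therefore contributes 0 modules to the trial data, and the set holds at most 45 app participants and 0 of 45 controls. The group-by-time term of the linear mixed model needs both arms, so it cannot be estimated. The app is free to download and no block on controls is described, so a control who obtained it early could qualify; the only controls in the set would then be those who departed from their assignment. This step needs no assumption.

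**2. The plan's own sample size.** Inputs from Power Calculation: f = 0.155, 2 groups, m = 3 time points, two-sided 5%, 90% power, N = 90. Assumed, because not stated: correlation between repeated measures 0.5 and sphericity.
- Interaction test: λ = f²·N·m/(1−ρ) = 0.024025 × 90 × 3/0.5 = 12.97, with 2 and 176 degrees of freedom.
- Power is 90.2% and the required N is 90, so the stated figure reproduces.

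**3. Size of a completers-versus-all-controls set.** N in λ is replaced by 4n₁n₂/(n₁+n₂), with n₂ = 45.

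| Completion | Completers of 45 | Effective N | Power |
|---|---|---|---|
| 0.5% | 0.2, so about 0 | – | – |
| 28.7% | 12.9, so 13 | 40.3 | 56% |
| 50% (assumed) | 22 | 59.1 | 74% |
| 75% (assumed) | 34 | 77.5 | 85% |

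**4. Selection bias with no true effect.** Let r be the assumed correlation between the propensity to complete and the follow-up outcome, and p the completion proportion. The expected excess among completers is r·φ(c)/p, where c is the normal cut-off leaving p above it.
- p = 0.287: φ(c)/p = 1.187, so 0.24 SD at r = 0.2 and 0.36 SD at r = 0.3.
- p = 0.5: φ(c)/p = 0.798, so 0.16 SD at r = 0.2 and 0.24 SD at r = 0.3.

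False-positive rates were simulated with 45 per arm and two-sided t tests at 5%. The test of change from baseline stands in for the planned interaction and assumes a baseline-to-follow-up correlation of 0.5.

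| Completion, r | Groups compared at follow-up | Change, selection on a stable trait | Change, selection on the later score |
|---|---|---|---|
| 28.7%, 0.2 | 11% | 5% | 7% |
| 28.7%, 0.3 | 19–20% | 5% | 9% |
| 50%, 0.2 | 9% | 5% | 6% |
| 50%, 0.3 | 15% | 5% | 7% |
| 75%, 0.3 | 8–9% | 5% | 6% |

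A stable trait is already present at baseline, so it cancels from the change score (bias about 0). Selection on the later score leaves r·φ(c)/p × (1 − 0.5): at 28.7% completion, 0.12 SD for r = 0.2 and 0.18 SD for r = 0.3.

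**The case against.** The strongest reply is that the main planned test is the group-by-time interaction, which uses baseline. If completers differ by a stable trait such as motivation, the interaction is not biased. This stands: a reader might infer that the 9% to 20% rates apply to the planned interaction, and they do not. They apply to comparisons of the groups at a single follow-up, which the plan includes only as post hoc tests. Selection on improvement itself would not cancel in either analysis.

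Four further points limit what can be said.
- A reader might take 0 to 13 completers of 45 as the trial's own expectation. The completion range comes from other interventions and is cited as the reason for designing a one-week app; the trial also uses push notifications, emails and a text message. It is a pessimistic scenario.
- A reader might infer that the per-protocol analysis has equal standing with ITT. The article says only that both will be done, names ITT first and ranks neither.
- A reader might say that non-responders are removed from one arm only. Someone who answers no follow-up contributes no follow-up outcome in either arm. The asymmetry concerns app participants who give outcomes but no completion report, and baseline-only participants, whom the ITT mixed model keeps.
- The article discloses its reliance on self-reported engagement as a limitation.

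It can also be argued that the control-arm criterion belongs in a fuller document. That does not answer the point: the article states a rule, and the stated rule fails under the article's own design.

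**Conclusion.** The concern holds. As defined, the per-protocol set contains no protocol-following controls and cannot yield the planned between-group effect; this follows from the text alone. Filtering only the app arm gives an estimable but non-randomised comparison.

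The bias is conditional. Over 28.7% to 50% completion and r from 0.2 to 0.3, it is about 0.16 to 0.36 SD for groups compared at follow-up, with false-positive rates of about 9% to 20%. For the planned change-over-time test the rate is about 5% under stable-trait selection and about 6% to 9% under selection on the later score. The correlations, including the 0.5 between baseline and follow-up, are assumptions, and the completion rates are borrowed or assumed.

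The documents do not support reading this as a flaw in the trial's whole efficacy conclusion. ITT is planned and intact, and the trial claims only preliminary effectiveness. Severity: should-fix.

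**What to change.** State that ITT is the sole basis for the efficacy conclusion. Then replace the per-protocol rule with one of the following.

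1. **Arm-specific criteria.** App arm: reported completion of all seven modules. Control arm: assessed, with no app use before the 3-month assessment. Label the analysis supportive and subject to selection. Controls would have to be asked about app use.
2. **Complier-average causal effect.** Use randomised arm as the instrument for the number of modules completed. This is preferable to an all-seven indicator, because partial completion may itself have an effect, which would break the exclusion restriction.

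Under either option, give a stated rule for missing outcomes and for unreported completion (for example, count non-reporters as non-completers), with a sensitivity analysis that reverses it. Two-stage least squares does not by itself keep participants who lack a follow-up outcome.

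The cost is plan wording and, for option 2, one extra model. That model has a wider interval than the naive completer contrast, an exclusion restriction to state, and a weak instrument if completion is very low. With 45 per arm and the all-seven indicator, the first-stage F is 44·p/(1−p): 1.0 with 1 completer, 5.5 with 5 and 17.9 with 13.
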